### Control Group

Participants are educated on the benefits of exercise for people living with HIV but are asked not to engage in any form of structured physical activity for the corresponding 12-week period. The first education session occurs while the exercise participants are being moved to the trial site, which serves to distract the control group participants. The second education session takes place 6 weeks into the intervention, during which participants are asked if they have engaged in any structured physical activity and if yes, they are asked to quantify the intensity and time. We encourage control group participants to abstain from structured physical activity.

### Criteria for Discontinuing or Modifying Allocated Interventions

The aerobic exercise intervention is discontinued or modified if participants experience exercise-related angina pectoralis or shortness of breath during 2 successive sessions, exercise-induced tachycardia during an exercise session, severe illness capable of affecting the participant’s exercise capacity, complaints of worsening cognitive ability, or if participants request to discontinue or modify the exercise intensity.

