### Eligibility Criteria

We included patients if they met the following criteria: diagnosed with HAND and physically inactive (sedentary, <2 hours of exercise per week; ready to exercise upon assessment, not engaged in regular exercise for approximately 3 months before the study). Patients were excluded if they were older than 65 years; had uncontrolled hypertension (blood pressure [BP] ˃140/90 mm Hg), deafness, severe eye impairment, physical disability, history of traumatic brain injury, psychiatric illness, recent focal neurological deficit, active depression, alcohol or substance abuse, musculoskeletal injury, or acute illness capable of hampering exercise performance; pregnancy; or had angina pectoralis and/or shortness of breath at rest or during exercise. We excluded participants on cognition-enhancing drugs such as eugeroics, attention deficit/hyperactive disorder medications, and nootropic supplements.

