### Exercise Intervention

Participants in the aerobic exercise group exercise on a bicycle ergometer at a low intensity of between 60% and 80% of their HRmax as recommended by the American College of Sports Medicine (ACSM) [49]. Participants train 3 times a week for 12 weeks. Initially, participants train at 60% of HRmax, and this is increased after 4 weeks to 80% HR_max_ for the remainder of the training period. Each training session consists of 20 minutes to 30 minutes of aerobic exercise in the first 4 weeks depending on the patient’s tolerance. After the first 4 weeks, training sessions are increased to 30 minutes to 45 minutes and further increased after the eighth week to 60 minutes for the remainder of the intervention. Participants are encouraged to give their best to the moderate-intensity exercise. Participants are prepared for exercise following the ACSM guidelines [46]. All fitness testing is performed by qualified physiotherapists.

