### Adverse Event Reporting and Harms

Participants are asked to report any adverse event following exercise. Adverse events are formally assessed every 2 weeks using an adverse event form piloted by the US Medical Device and Diagnostic Industry recommendations [87,88] (Multimedia Appendix 13). If an adverse event is reported, the patient is referred to their physician for immediate assessment of underlying cause and possible management. A physiotherapist treats cases of pain, lower back pain, fatigue, and muscle soreness and prescribes rest to the participants when necessary. In cases of spontaneous but mild adverse events, patients are given sufficient time to rest, after which a therapist decides if the participant is fit to continue the scheduled exercise.

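### Angina during training must recur in 2 successive sessions before exercise is discontinued or modified; one episode should be enough

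*Protocol article*

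**What the plan says.** The protocol article's section Criteria for Discontinuing or Modifying Allocated Interventions sets the rule: "The aerobic exercise intervention is discontinued or modified if participants experience exercise-related angina pectoralis or shortness of breath during 2 successive sessions". The next item in the same sentence is "exercise-induced tachycardia during an exercise session", which needs one session only. The remaining items (severe illness affecting exercise capacity, complaints of worsening cognition, and the participant's own request) carry no repeat condition.

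Eligibility Criteria excludes patients who "had angina pectoralis and/or shortness of breath at rest or during exercise", again with no repeat condition.

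Adverse Event Reporting and Harms adds a separate route: "If an adverse event is reported, the patient is referred to their physician for immediate assessment of underlying cause and possible management". For spontaneous but mild events it provides rest, "after which a therapist decides if the participant is fit to continue the scheduled exercise".

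Exercise Intervention gives the load. "Participants train 3 times a week for 12 weeks". Intensity starts at 60% of maximum heart rate and goes to 80% after week 4. Sessions last 20 to 30 minutes at first; later, "training sessions are increased to 30 minutes to 45 minutes and further increased after the eighth week to 60 minutes".

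**The concern.** New chest pain on effort calls for action the first time it appears. The written criterion asks for it in two sessions running before the programme is discontinued or even modified. Under that criterion alone, a first episode does not call for a lower workload. The threshold also sits badly with the protocol's own standards: one session of tachycardia is enough, and angina would have kept the same person out of the trial.

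What is at stake is participant safety. No bias in an estimate and no loss of power is claimed.

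**Working it through.** The article states no figure to reproduce. The check sets the sections side by side and then counts sessions.

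**Comparison of triggers**

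| Event | Where | Repeat needed? |
|---|---|---|
| Angina at entry | Eligibility Criteria | No; excluded |
| Angina in training | Discontinuing or modifying criteria | Yes; 2 successive sessions |
| Breathlessness in training | Same sentence | Yes; 2 successive sessions |
| Tachycardia in training | Same sentence | No; one session |
| Severe illness, worsening cognition, request | Same sentence | No |
| Any reported adverse event | Adverse Event Reporting and Harms | No; physician referral |

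Only angina and breathlessness have to recur, and the article gives no reason for treating angina more leniently than tachycardia. The 2-session phrase could be attached to breathlessness alone, but the sentence does not say so. A stopping rule that leaves this open would need the same clarification.

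**What the threshold means in the schedule** (inputs from Exercise Intervention)

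1. Sessions: 3 per week × 12 weeks = 36, so there are 36 − 1 = 35 transitions from one session to the next.
2. After a first episode of angina, the criterion for that symptom cannot be met before the next session. That session would be:
   - 20 to 30 minutes at 60% of maximum heart rate in weeks 1 to 4;
   - 30 to 45 minutes at 80% in weeks 5 to 8;
   - 60 minutes at 80% in weeks 9 to 12.
3. First load step: week 4 ends at session 3 × 4 = 12, so session 13 is the first at 80% and the first of 30 to 45 minutes.
4. Second load step: week 8 ends at session 3 × 8 = 24, so session 25 is the first of 60 minutes.
5. A scheduled step therefore falls at 2 of 35 transitions (12 to 13 and 24 to 25), or 2/35 = 5.7%. At the other 33 the next session has the same scheduled load, apart from variation within the stated duration ranges.
6. Time to the next session: 7 days / 3 = 2.3 days on average, so usually 2 to 3 days if sessions are spread over the week. The spacing is an assumption; the article does not fix the days.

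These counts describe how the rule works. Without a rate of angina they do not give an expected number of events.

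**The case against.** The strongest reply is that a first episode is not ignored. The adverse event section refers any reported event for immediate assessment without asking for a repeat. With 2 to 3 days between sessions, that assessment would ordinarily come before the next one. A first angina episode could also be handled as severe illness, or the participant could ask to stop, and nothing forbids earlier action. Entrants with these symptoms are excluded, and the entry test works toward 70% of heart rate reserve or 85% of age-predicted maximum heart rate. All of this stands and lowers the risk. It does not change a threshold that is written down explicitly, so condensation into an article does not explain it.

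Some breathlessness is also to be expected in sedentary participants working at up to 80% of maximum heart rate. Asking for persistence over two sessions is defensible for that symptom. This stands, and the point is therefore limited to angina.

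A reader might infer three stronger things that the article does not support:

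- **That participants must ride on through chest pain.** The criterion concerns changing the programme and does not direct conduct within a session.
- **That the referral is defective because it does not say training is held until the assessment.** This is silence on a procedure that an article commonly leaves to the full protocol, which is not shown.
- **That a therapist may clear a participant after angina.** That decision is confined to spontaneous, mild events, and nothing in the text classes exertional angina as mild.

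**Conclusion.** The point holds for angina. The stated criterion requires two successive sessions with angina before exercise is discontinued or modified, which is out of line with the tachycardia criterion beside it and with the entry exclusion. It rests on the natural reading of the sentence, under which the 2-session condition covers both symptoms.

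The size is modest. The separate physician referral covers a first reported episode, a scheduled rise in load coincides with the next session at only 2 of 35 transitions, and no event rate is given or assumed. It is a worthwhile safety correction to one clause and does not show that participants were left unprotected.

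**What to change.** In Criteria for Discontinuing or Modifying Allocated Interventions, remove the 2-session condition for angina or chest pain. State that a first episode ends the session and that training resumes only after the physician assessment already provided for under Adverse Event Reporting and Harms. The 2-session condition may stay for ordinary exertional breathlessness.

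The cost is one clause and a few referrals that find nothing. Sessions missed per episode:

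- none if the assessment comes before the next session (0/36 = 0%);
- one if it does not (1/36 = 2.8%);
- three for a one-week wait (3/36 = 8.3%).

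The Results section says enrollment was completed in May 2021, so training may already be over. In that case the remedy is reporting: for each angina episode, state whether a physician assessed the participant before the next session.

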### Strategies to Improve Adherence to Interventions

During the pilot study, we noted that one of the major challenges faced by our prospective participants was increased transportation costs and the attendant opportunistic costs of participants who will not be able to work due to the study. Participants are given a sum of N2000 (US $4.86) every 2 weeks to cover transport costs. We call participants on the day before their exercise session to remind them of their appointment. Participants are called by telephone if they fail to show up for training or a periodic appointment to ascertain the reason for their absence and improve compliance.

### Relevant Concomitant Care Permitted or Prohibited During the Trial

Participants continue with their ART. Participants are discouraged from continuing any medication not prescribed by a physician. Prospective participants are allowed a washout period of 2 weeks before being eligible to continue.

### Study Outcomes

The primary outcomes include neurocognitive performance, prevalence of HAND, viral load, and CD4 count. The secondary outcomes include maximum oxygen uptake (VO_2_), QoL, activity limitation, and participation restriction. Potential confounding variables include age, sex, level of education, vaccination, history of virologic failure, level of ART adherence, exercise adherence, ART regimen, ovulation status, history of recent vaccination, and seasonality. These variables will be measured at baseline, after 12 weeks, and 3 months after the intervention. Their change will be measured over time. Aggregation parameters will include proportion, mean, or median depending on how the data are distributed.

### Participant Timeline

The proposed timeline for the study and planned elements is shown in Figure 1. All prospective participants were identified in a pilot study. Baseline assessments were conducted from the end of January 2021 to mid-February 2021 and covered neurocognitive performance, BP, HR, respiratory rate, assessment of physical activity readiness, QoL, CD4 count, viral load, and activity limitation and social participation. Before the intervention, all participants undergo an exercise stress test. The aerobic exercise intervention starts a day after exercise testing and lasts for 12 weeks. Following the 12-week aerobic intervention, postexercise assessments are conducted.

**Figure 1 figure1:**
[figure not shown]
Proposed timeline for the randomized controlled trial for measuring the efficacy of exercise for rehabilitating symptoms associated with HIV-associated neurocognitive disorder (HAND) in people living with HIV.

### Sample Size

An estimated sample size of 68 (34 in each group) will have 90% power to detect a difference in means of 13.4 (the difference between a Group 1 mean, µ_1_, of 56 and a Group 2 mean, µ_2_, of 42.6) assuming that the common SD is 16.67 using a 2-group *t* test with a 5% 2-sided significance level.

### Neuropsychological Screening

The principal investigator (who is a physiotherapist working with people living with HIV and neurological conditions), a clinical psychologist, and a neurologist (who is a specialized medical doctor) conduct the neuropsychological screening, which is conducted in 3 stages. First, we conduct a brief neuromedical screening using a pilot assessment guide; then, we administer the neuropsychological instruments and, finally, assess the subjective symptoms of HAND such as difficulty remembering recent events (people, conversations, names, commitments, where things are placed), understanding conversation or reading materials, word finding, planning activities, problem solving, concentrating, thinking clearly or logically, finding his or her way about, calculating, and following direction or instruction.

We administer neuropsychological instruments chosen for their simplicity and ease of administration in any language. Only the Hopkins Verbal Learning Test-Revised (HVLT-R) and Controlled Oral Word Association Test (COWAT) require understanding of some English words. These tests were extracted from the international neurobehavioral test battery used by the HIV Neurobehavioral Research Center [1] and a recent clinical trial on HAND [50,51]. These tests are sensitive to HAND in Nigeria [52,53]. We first screen for probable dementia using the International HIV Dementia Scale (IHDS). Confirmatory neuropsychological tests are administered in the following order: first, we administer the HVLT-R immediate recall (duration 3-5 minutes). After waiting 20 minutes to 25 minutes to administer the second part of the HVLT-R, we administer the Trail Making Test (TMT)-A and -B (5-10 minutes), verbal fluency (3-8 minutes), and the Digit Span Test (5-10 minutes). We then administer the HVLT-R delay recall. We also assess neurocognitive performance in line with the 2007 modified American Academy of Neurology criteria, also known as the Frascati criteria [1,54]. We will convert the raw scale scores using a clinical rating algorithm, to sum the scores to obtain an overall score for each participant. The latter will be used for covariate analysis, if needed.

### Tests

#### Beck Depression Inventory

The Beck Depression Inventory (BDI) [55] measures characteristic attitudes and symptoms of depression using a 21-item self-report rating inventory (Multimedia Appendix 1). The BDI takes approximately 10 minutes to complete and requires a fifth- to sixth-grade reading level to adequately understand the questions. Internal consistency ranges from 0.73 to 0.92, with a mean of 0.86 [56]. The BDI has demonstrated high internal consistency, with alpha coefficients of 0.86 and 0.81 for psychiatric and nonpsychiatric populations, respectively [57]. A score ≥17 indicates borderline clinical depression.

#### Alcohol Use Disorder Identification Test

The Alcohol Use Disorder Identification Test (AUDIT) [58] is approved by the World Health Organization (WHO) to assess intoxication or withdrawal (Multimedia Appendix 2). The AUDIT is comprised of 10 items, and a score ≥8 indicates alcohol intoxication or withdrawal. Patients with scores >8 were excluded from the study [12]. It takes 2 minutes to 4 minutes to complete.

#### Drug Abuse Screening Test

The Drug Abuse Screening Test [59] is a valid and reliable instrument consisting of 10 items (Multimedia Appendix 3). Patients who score ≥3 are suspected of drug abuse and were excluded from the study. It takes approximately 5 minutes to administer.

#### International HIV Dementia Scale

We screen HIV-positive patients for dementia and cognitive impairment using the IHDS [60] (Multimedia Appendix 4). The IHDS tests registration, recall, motor function, and information processing. The IHDS has a sensitivity and specificity of 74% and 46%, respectively, at a cutoff point of 9.5. The test does not require any special instruments except a timer or wristwatch and can be easily administered by other health workers, not necessarily by a physician. The IHDS is also free of cultural bias and can be used in many resource-limited countries.

#### Controlled Oral Word Association Test

We use the COWAT [61] to assess verbal fluency using FAS letter fluency—number of words generated (Multimedia Appendix 5). Verbal fluency measures cognitive function that facilitates information retrieval from memory, and the verbal fluency test evaluates an individual's ability to retrieve specific information within restricted search parameters [62]. This test requires the individual to name as many words as possible that begin with a given letter (ie, F, A, and S). Each letter is allotted 60 seconds. Individuals cannot use proper names or numbers and cannot use words with different tenses or endings once the root word has been given. They have to do it as quickly as possible, and the number of words produced during 1 minute is scored for both phonemic and semantic verbal fluency [62]. The test takes 3 minutes to 8 minutes to complete. The score equals the mean number of words uttered in the 3 trials corresponding to each initial letter [63]. This test does not require special instrumentation.

#### Hopkins Verbal Learning Test-Revised

The HVLT-R [64] is used to assess verbal learning and memory or recall (Multimedia Appendix 6). The HVLT-R is simple to administer and is similar to the California Verbal Learning Test [65]. An assessor gives the patient a list of 12 words with an embedded semantic structure (4 categories of 3 words each). The assessor reads the list to the patient, who is then asked to repeat as many words as possible in any order (free recall). This process is repeated 3 times, which represents the 3 learning trials. After a 25-minute break, the patient is again asked to remember as many of the words as possible in any order. The patient’s semantic strategy is evaluated by examining the degree to which words are semantically clustered during the 3 learning trials. In the standard administration, items from the same category are not presented together, and subjects are not informed of the semantic organization. The HVLT-R’s 3 learning trials and delay recall trial are scored separately. The 3 learning trial scores (number of correct words) are summed to yield a total score. Overall, this test takes 28 minutes to 30 minutes. This test does not require instrumentation.

#### Trail Making Test-A and -B

The TMT is a 2-in-1, sensitive, paper-and-pencil measure of information processing speed and executive function [66,67] (Multimedia Appendix 7). The TMT consists of 2 parts (TMT-A and TMT-B). The TMT-A consists of a standardized page on which the numbers 1 to 25 are scattered within circles, and the participants are asked to connect the numbers in order as quickly as possible. Similarly, the TMT-B consists of a standardized page that includes the numbers 1 to 13 and the letters A to L. The participants are instructed to draw lines connecting numbers and letters in order, alternating numbers and letters. Before starting the test, participants are allowed to practice on 6 items to make sure that they understand both tasks. When a participant makes an error during the test, the examiner points it out, explains, and then guides the participant to correctly complete the circles, after which the participants are requested to continue with the task. A maximum time of 300 seconds is allowed before discontinuing the test. Direct scores of TMT will be the time in seconds taken to complete each task (-A and -B). This test takes 5 minutes to 10 minutes.

#### Digit Span Test

The digit span test (DST) [68] is a pencil-and-paper instrument and evaluates auditory attentional capacity and working memory for orally presented information (Multimedia Appendix 8). In this study, the DST is used to assess attention and working memory. The DST was originally developed for people between 18 years and 97 years old and is appropriate for use in this study. Participants are asked to repeat series of digits that become gradually longer. The maximum digit span that the participants are able to repeat in direct and reverse orders constitutes the forward (DST-f) and backward (DST-b) scores, respectively [51,68]. This test should be completed in 10 minutes to 15 minutes.

#### The Lawton Instrumental Activities of Daily Living Scale

The Lawton Instrumental Activities of Daily Living Scale is a valid and sensitive measure of instrumental activities of daily living and is comprised of 8 items (Multimedia Appendix 9). Scores <8 may indicate functional impairment [9]. This test takes 3 minutes to 5 minutes to complete.

#### The WHO Quality of Life-BREF

We use the short form of the World Health Organization Quality of Life (WHOQOL)-BREF, which has been validated in diverse settings, including African countries, and is based on a well-classified definition of QoL (Multimedia Appendix 10). It is comprised of physical, psychological, social, and environment domains. The WHOQOL-BREF is a recommended instrument for people living with HIV infection [69,70]. The WHOQOL-BREF has an internal consistency of α=0.74-0.85 and test-retest reliability of rho=0.64-0.79 [71]. Each of the 4 domains is measured on a 5-point Likert scale: 1 indicates low perception, and 5 indicates high perception [69]. The WHOQOL-BREF measures the perceived QoL and hence contains items asking how patients felt about different facets of life in the week before being assessed.

